**Figure 2 figure2:**
[figure not shown]
HEART Pathway algorithm.

### Data Collection

The effectiveness of the HEART Pathway will be assessed using electronic outcome surveillance. EMR data will be collected on all patients with chest pain. Insurance claims data will be collected on patients with Medicaid, MedCost, and BCBS of North Carolina. Data will include patient demographics, past medical history, cardiovascular risk factors, ECG results, troponin results, HEART score and HEART Pathway assessments, ED and discharge diagnoses, disposition, index visit length of stay, objective cardiac testing (stress testing or angiography) at the index visit or within 30 days, recurrent ED visits, readmissions, and myocardial infarction (MI) or death within the follow-up period. Data extraction from the EMR data warehouse (Clarity) will be automated and programmed to pull prespecified data points into our database on patients meeting eligibility criteria on a weekly or monthly basis (Figure 3). Electronic surveillance leverages our informatics strengths and data sharing relationships with insurers, to provide efficient and accurate outcome data. Data accuracy is enhanced by avoiding recall bias inherent in other follow-up methods such as telephone calls. Electronic surveillance also improves feasibility by allowing programmable follow-up on a large number of patients at a low cost. Inclusion of Medicaid patient claims should ensure that our data surveillance includes economically disadvantaged patients and is generalizable to the patient populations of other hospitals. Any discrepancies between sources of data will be adjudicated by study investigators blinded to patient pre- or post-intervention cohort participation. Based on prior studies, we expect 80% of patients to have follow-up data from the EMR or insurer claims. The Social Security Death Master File will be used to search for participants without follow-up data.

The preintervention cohort will be identified using the same inclusion criteria (aged ≥ 21 years with a complaint of chest pain and a troponin ordered without STEMI on ECG) for 1 year prior to integration of the HEART Pathway into cardiovascular care delivery at Wake Forest Baptist Health. The same data elements described above will be abstracted from the EMR and claims databases from BCBS, MedCost, and Medicaid.

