### Study Timeline

Pre- and post-HEART Pathway ADP implementation cohorts will each accrue patients with acute chest pain for 1 year, with a 3-month wash-in period (Figure 1). Data will be collected electronically from all patients using health system electronic medical records (EMRs), and claims data from insurers will be used on a subset of patients insured by Blue Cross Blue Shield (BCBS) of North Carolina (the largest insurer in the state), MedCost, or North Carolina Medicaid.

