### Statistical Analyses

Logistic regression models, which include potential patient-level confounders such as age, sex, race, ethnicity, insurance status, and ACS risk factors in addition to the intervention indicator, will be used to assess the effect of the HEART Pathway intervention on hospitalizations (and other dichotomous outcomes such as objective cardiac testing and recurrent ED visits). As secular trends represent a threat to internal validity (observed differences between groups could be from time trends rather than the intervention), we will include the time since the start of the study in the models, as well as the time by intervention interaction. This will allow us to assess the effect of the HEART Pathway implementation on the proportion of patients hospitalized, as well as its effect on the time trend after implementation.

Continuous outcomes will be analyzed using multiple linear regression models including potential confounders, time, the intervention indicator (pre- or post-HEART Pathway implementation), and the time by intervention interaction as described above. LOS tends to be skewed, so we will use some transformation (log, rank, etc) in the analyses if necessary. Residuals will be examined to ensure the model assumptions (linearity, homoscedasticity, and normality) are met. Not all patients will have electronic follow-up data. The default assumption will be that patients without follow-up data from the EMR, insurers, or Social Security Death Masterfile did not suffer adverse events. Sensitivity analyses will be used to assess the impact of missing data on our results. The analyses will be repeated assuming all patients with missing follow-up data had follow-up events (hospitalization, cardiac testing, etc). Multiple imputation will be used to conduct sensitivity analyses that generate complete datasets under a variety of assumptions regarding the rates of outcomes in the two periods. All analyses will be performed using SAS 9.4 (Cary, NC). *P*<0.05 will be considered significant.

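### For patients without claims data, events at other hospitals have no stated route into the outcomes or the sensitivity analyses; the missed-adverse-event and recurrent-care counts are most exposed

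*Protocol article*

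**What the plan says.** All places are in the Protocol article.

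- **Sources.** Study Timeline draws the health system's EMR for every patient and adds that "claims data from insurers will be used on a subset of patients". Data Collection names the insurers: "Insurance claims data will be collected on patients with Medicaid, MedCost, and BCBS of North Carolina".
- **Expected follow-up.** "Based on prior studies, we expect 80% of patients to have follow-up data from the EMR or insurer claims" (Data Collection). Sample Size carries this forward as 4000 patients per group and bases the safety precision of ±0.33% on it.
- **Deaths.** "The Social Security Death Master File will be used to search for participants without follow-up data" (Data Collection).
- **Missing follow-up.** "The default assumption will be that patients without follow-up data from the EMR, insurers, or Social Security Death Masterfile did not suffer adverse events" (Statistical Analyses). Against this default, "The analyses will be repeated assuming all patients with missing follow-up data had follow-up events", and multiple imputation varies the assumed outcome rates in the two periods.
- **Outcomes.** Outcome Measures sets a window of the index visit plus 30 days. It defines missed adverse events as death or MI in patients sent home from the ED without objective testing, and lists recurrent ED visits and nonindex admissions as secondary outcomes.
- **Limitations** concedes that electronic surveillance may raise loss to follow-up. It does not mention care received at other hospitals.

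**The concern.** The point concerns patients counted as followed, not the 20% expected to lack follow-up. For someone outside the three insurers, the only stated window on the 30 days is this system's EMR. If that patient has some follow-up here but an MI, admission or test elsewhere, the study sees no event. The patient is not missing, so the analyses built for missing data do not question that value.

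The error would not be equal in the two periods. An event during the index stay is always seen. One after ED discharge is seen only if the patient returns to this system or has claims. Implementation is intended to raise the share sent home, so the post-implementation period relies more on the weaker source. At stake is the claim that utilization falls without loss of safety.

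**Working it through.** **1. Does any stated safeguard reach an event-free, EMR-only patient who is counted as followed?**

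- All-events repeat: restricted to patients with missing follow-up. No.
- Multiple imputation: described within the same missing-data plan. Not as described.
- Death file: restricted to participants without follow-up data. No, so a death elsewhere can also be missed.
- Blinded adjudication: resolves discrepancies between sources. With a single source there is none to resolve.

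**2. The plan's own figure.** Precision at n = 4000 and p = 1%:
1.96 × √(0.01 × 0.99 / 4000) = ±0.308%; the exact (Clopper-Pearson) half-width is ±0.322%. The stated ±0.33% is not reproduced exactly but is slightly conservative, which does not affect this point. What matters is that it treats all 4000 as fully observed.

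**3. Unseen share of post-discharge events.** Let c be the claims-covered share of followed patients and o the share of post-discharge events treated elsewhere. Neither is in the documents; both are assumed, with claims taken to detect everything. Unseen share u = (1 − c) × o:

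| c | o = 10% | 20% | 30% | 40% |
|---|---|---|---|---|
| 30% | 7% | 14% | 21% | 28% |
| 50% | 5% | 10% | 15% | 20% |
| 70% | 3% | 6% | 9% | 12% |

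The range is 3% to 28%. For events during the index stay, u = 0.

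**4. Bias in the death/MI comparison.** Take a true rate of 1% in both periods (the plan's planning rate), with the post-discharge share of events rising from 20% to 30-40% (assumed). Bias = −(rise in share) × 1% × u:
- smallest: 0.10 × 1% × 0.03 = 0.003 points
- largest: 0.20 × 1% × 0.28 = 0.056 points

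For comparison, the 95% half-width for a difference between two periods of 4000 is √2 × 0.308 = 0.44 points.

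**5. Bias in 30-day hospitalization.** With index rate i and later admission in a fraction r of those sent home (same r in both periods), the true rate is i + (1 − i)r and the observed rate is i + (1 − i)r(1 − u). The pre-post difference is therefore biased by −(fall in i) × r × u. Take i from 53% (Sample Size) to 48% or 43%, and r = 3-10% (the falls and r are assumed):
- smallest: 0.05 × 0.03 × 0.03 = 0.0045%, under 0.01 points
- largest: 0.10 × 0.10 × 0.28 = 0.28 points

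The bias scales with the fall in i. At the 21.3-point early-discharge difference of the earlier randomized trial (Preliminary Data) the upper end is 0.213 × 0.10 × 0.28 = 0.60 points. In every case it is at most 0.10 × 0.28 = 2.8% of the index fall, and zero if i does not change. With 4000 per period, 90% power is reached at a reduction of about 3.6 points.

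**6. Outcomes made up of post-discharge events.** Missed adverse events and nonindex admissions occur essentially after discharge, as do recurrent ED visits if visits to any ED are meant. Here u is not diluted by index-stay events, so the counts are low by the full 3-28% on these assumptions.

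**7. Precision in a claims-covered analysis.** If 30-70% of 5000 per period are covered, n = 1500 to 3500, and the step 2 formula gives ±0.50% to ±0.33% at a 1% rate.

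**The case against.** **The follow-up rule is not spelled out.** A reader might infer that any EMR record makes a patient followed. The article does not say so. Every patient has an index EMR record, so that rule would give 100%, not 80%. How completeness is defined may be left to the full protocol or analysis plan, and the data-flow figure is not shown. This stands: the article does not fix which EMR-only patients count as missing. But it does fix the limits of claims coverage, the scope of the death search and the target of the sensitivity analyses, and these leave the gap.

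**Relocation of events is inferred.** A reader might infer that the pathway demonstrably moves events from hospital to home. That follows from its purpose only. Early discharge requires a low score and negative serial troponins, and in the earlier randomized trial no patient identified for early discharge had an adverse cardiac event within 30 days. Few deaths or MIs may move. For testing, the aim is to avoid tests, not to relocate them. This stands and limits the size, not the mechanism.

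**The unseen share is not the bias.** A reader might take 28% as the distortion of the treatment comparison. It is the upper assumed share of post-discharge events unseen; the pre-post bias is far smaller, because the primary outcome is mostly index hospitalization, which is always captured. This also stands.

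**Conclusion.** The gap follows from the text. Events at other hospitals in patients outside the three insurers have no stated route into the data, and the planned sensitivity analyses and death search, as described, do not reach such patients once they count as followed. Any under-capture would tend to favour the pathway.

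The effect on the main comparisons is small: up to about 0.3 points on 30-day hospitalization for index falls of up to 10 points, and about 0.06 points on a 1% death/MI rate. The documents give no ground for saying that the primary conclusion would reverse. The material exposure is to missed adverse events, recurrent ED visits and nonindex admissions, where 3-28% could go uncounted. Missed adverse events matter most, since they bear directly on the safety of sending patients home untested.

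These sizes rest on assumed values for claims coverage, care elsewhere, the timing of events and later admissions; only the 53%, the 1%, the patient numbers and the 21.3 points come from the documents. Full capture by claims is itself an assumption.

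**What to change.** - **Data Collection:** search the Social Security Death Master File for all patients in both periods, not only those without follow-up data.
- **Statistical Analyses:** add a sensitivity analysis that repeats the primary outcome, death/MI and missed adverse events in patients with insurer enrolment through day 30 (or death) in both periods, reported beside the whole-cohort result.

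Two tempting alternatives should be avoided. Completeness should not depend on whether an outcome was observed, because that selects on the outcome. Nor should event-free EMR-only patients enter the all-events repeat. With 30-70% claims-covered, that would assign death or MI to most of the other 30-70% of followed patients, against an expected 1%. It would also shrink a true 5-point fall in hospitalization to between 0.3 × 5 = 1.5 and 0.7 × 5 = 3.5 points by construction.

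**Cost:** a wider death-file search, an enrolment flag from insurers that already share data, and one repeated set of analyses. The claims-covered analysis is smaller, less precise (about ±0.50% to ±0.33% at a 1% event rate if 30-70% of 5000 are covered) and limited to three insurers, so it supports the whole-cohort result and does not replace it.

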**Figure 3 figure3:**
[figure not shown]
Flow of data into the HEART Pathway Implementation Database.

### Outcome Measures

Pre- and post-HEART Pathway cohorts will be compared for safety and health care utilization outcomes. The primary outcome will be hospitalization rate at 30 days for patients presenting with acute chest pain. Secondary outcomes will include index hospitalization rate, index and 30-day objective cardiac testing, hospital length of stay (LOS), recurrent ED visits, and nonindex admissions for chest pain. Outcomes will be assessed during the index visit and for 30 days thereafter.

Hospitalization will be defined as an inpatient admission or observation stay. Objective cardiac testing will be defined by any stress testing modality, coronary computed tomography angiography, or invasive coronary angiography. The modalities routinely available at Wake Forest Baptist Health include exercise ECG, exercise stress echocardiogram, dobutamine stress echocardiogram, coronary computed tomography angiography, stress nuclear imaging, stress cardiac magnetic resonance imaging, or invasive coronary angiography. LOS will be the time from ED arrival to hospital discharge for all patients, whether admitted or not. A recurrent visit to the ED will be defined as any patient revisiting the ED with chest pain or other symptoms suggestive of ACS within the 30-day follow-up period.

Safety outcomes will include death and acute MI within 30 days. Missed adverse events will be defined as death or MI occurring in patients discharged from the ED without objective cardiac testing. The definition of MI will be based on the Third Universal Definition of MI, which includes a rising or falling pattern of troponin with a cutoff representing the 99th percentile reference value with a coefficient of variation <10% [20].

### Statistical Analyses

Logistic regression models, which include potential patient-level confounders such as age, sex, race, ethnicity, insurance status, and ACS risk factors in addition to the intervention indicator, will be used to assess the effect of the HEART Pathway intervention on hospitalizations (and other dichotomous outcomes such as objective cardiac testing and recurrent ED visits). As secular trends represent a threat to internal validity (observed differences between groups could be from time trends rather than the intervention), we will include the time since the start of the study in the models, as well as the time by intervention interaction. This will allow us to assess the effect of the HEART Pathway implementation on the proportion of patients hospitalized, as well as its effect on the time trend after implementation.

Continuous outcomes will be analyzed using multiple linear regression models including potential confounders, time, the intervention indicator (pre- or post-HEART Pathway implementation), and the time by intervention interaction as described above. LOS tends to be skewed, so we will use some transformation (log, rank, etc) in the analyses if necessary. Residuals will be examined to ensure the model assumptions (linearity, homoscedasticity, and normality) are met. Not all patients will have electronic follow-up data. The default assumption will be that patients without follow-up data from the EMR, insurers, or Social Security Death Masterfile did not suffer adverse events. Sensitivity analyses will be used to assess the impact of missing data on our results. The analyses will be repeated assuming all patients with missing follow-up data had follow-up events (hospitalization, cardiac testing, etc). Multiple imputation will be used to conduct sensitivity analyses that generate complete datasets under a variety of assumptions regarding the rates of outcomes in the two periods. All analyses will be performed using SAS 9.4 (Cary, NC). *P*<0.05 will be considered significant.

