### Objectives and Hypotheses

In this paper, we describe the rationale and methods utilized to test the effectiveness of the HEART Pathway ADP within a health system consisting of three diverse hospital settings. We hypothesize that implementation of the HEART Pathway will significantly reduce hospitalizations and the rate of objective cardiac testing among low-risk patients, without increasing adverse cardiac events.

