## Methods

### Study Design

This prospective pre-post interrupted time series design compares the risk stratification of patients with acute chest pain before and after implementation of the HEART Pathway ADP. Wake Forest Baptist Health is a three-hospital academic health system located in the Piedmont Region of North Carolina. It consists of a large quaternary academic medical center with approximately 104,000 ED visits annually, a small community hospital with an annual ED volume of about 37,000 patients, and a free standing ED in an adjacent rural county with approximately 12,000 annual ED visits. This study is approved by the Internal Review Board of the sponsoring organization and is registered with clinicaltrials.gov (NCT02056964).

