### Sample Size

A sample size of approximately 10,000 patients, (5000) pre- and (5000) post-intervention, is anticipated. Based on prior studies it is expected that 80% (4000 patients/group) will have follow-up data from the EMR or insurer claims. With this sample size we will be able to estimate safety event rates for each study period to ±0.33% with 95% confidence (assuming an event rate of 1%). Based on our prior studies, we expect a hospitalization rate of 53% and an objective cardiac testing rate of 83% among hospitalized patients during the preintervention period [16,21]. This study will be adequately powered to detect reductions in hospitalization and objective cardiac testing rates of <5%, with 90% power at the 5% two-sided level of significance. We anticipate larger effects [16,17,22].

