### HEART Pathway Implementation

At the writing of this paper, data for this implementation study have been collected on >5000 patient encounters. The HEART Pathway has been fully integrated into health system EMRs, providing real-time decision support to our providers. Data infrastructure has been built such that patients meeting inclusion criteria are included in a registry, including 30-day electronic-surveillance data, which will be integrated with insurer claims data.

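### The outcome models name no hospital term although three very different sites contribute, and the article does not fix whether the unit is the patient or the encounter

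*Protocol article*

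**What the plan says.** **Model.** For hospitalization and the other binary outcomes, the Statistical Analyses section specifies logistic regression models that "include potential patient-level confounders such as age, sex, race, ethnicity, insurance status, and ACS risk factors in addition to the intervention indicator". To guard against secular trends it adds: "we will include the time since the start of the study in the models, as well as the time by intervention interaction". Continuous outcomes get linear regression with the same structure. Hospital is not mentioned.

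**Sites.** Objectives and Hypotheses places the study "within a health system consisting of three diverse hospital settings". Study Design describes "a large quaternary academic medical center with approximately 104,000 ED visits annually", a small community hospital with about 37,000 visits a year, and "a free standing ED in an adjacent rural county with approximately 12,000 annual ED visits".

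**Unit.** The Sample Size section plans "A sample size of approximately 10,000 patients", split equally between the periods. The Results section on implementation reports that "data for this implementation study have been collected on >5000 patient encounters", and the Abstract also counts encounters. Eligibility requires age 21 or over, chest pain, a troponin order and no STEMI. It has no first-visit rule. Outcome Measures defines a recurrent visit as "any patient revisiting the ED with chest pain or other symptoms suggestive of ACS within the 30-day follow-up period".

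**The concern.** The primary outcome is inpatient admission or an observation stay within 30 days. Its rate plausibly differs between a quaternary center, a community hospital and a free-standing ED. With no randomization, a pre-post difference can reflect who came to which site as well as what the pathway did. The article names secular trends as a threat and adjusts for time, but a change in site mix that coincides with implementation is not a smooth trend. It would appear in the intervention coefficient, which is the quantity of interest. Site is known for every visit, so this source of bias can be removed at almost no cost.

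The unit of analysis is a separate, secondary matter. A patient who returns within 30 days with chest pain and a new troponin order meets the entry criteria again. Nothing in the article prevents that return from being an outcome of the first visit and an index visit of its own, so that one admission or one MI could enter two records. No method for within-patient correlation is named. If all encounters were analysed with ordinary regression, the standard errors would be somewhat too small.

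**Working it through.** **1. The plan's own power figure.** Inputs from Sample Size: 53% hospitalized before implementation, 4000 followed per period, two-sided 5%, 90% power. A two-proportion calculation with pooled variance gives a detectable reduction of 3.6 points (3.2 with 5000 per period). Power for 53% against 48% is 99.4%. The claim of a detectable reduction below 5 points is reproduced.

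**2. Site shares.** From Study Design, 104,000 + 37,000 + 12,000 = 153,000 visits, so the shares are 104/153 = 68%, 37/153 = 24% and 12/153 = 8%. These are all-cause ED volumes, used here as a stand-in for chest-pain patients with a troponin order.

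**3. Effect of a mix shift on the crude rate.** Site admission rates are assumed, chosen to average close to the expected 53%. For 60/45/20%: 0.680 × 0.60 + 0.242 × 0.45 + 0.078 × 0.20 = 0.532.

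Volume leaving the academic center is split between the other two sites by their own volumes, 37:12. The average destination rate is (37 × 0.45 + 12 × 0.20)/49 = 38.9%. The spurious change is the shift × (60% − 38.9%):

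- 5-point shift: 0.05 × 21.1 = 1.1 points
- 10-point shift: 0.10 × 21.1 = 2.1 points

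The same calculation under other assumed rates:

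| Assumed site rates | Overall | Destination rate | 5-point shift | 10-point shift |
|---|---|---|---|---|
| 60/45/20% | 53.2% | 38.9% | 1.1 | 2.1 |
| 58/45/35% | 53.1% | 42.6% | 0.8 | 1.5 |
| 55/50/45% | 53.0% | 48.8% | 0.3 | 0.6 |
| 60/40/25% | 52.4% | 36.3% | 1.2 | 2.4 |

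An equal split of the diverted volume would give 1.4 to 2.8 points for the first row, but it sends an implausibly large part to the smallest site. For scale, 2.1 points is 2.1/3.6 = 58% of the detectable reduction in step 1.

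These are crude-rate shifts. They approximate the bias in the planned estimate only for a change in mix that is abrupt at implementation and not explained by the patient covariates.

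**4. Repeat visits.** The article gives neither a repeat share nor a within-patient correlation, so both are assumed. Let a fraction r of encounters be second visits, with at most two per patient. Then Σm²/Σm = 1 + 2r, and the design effect is 1 + (Σm²/Σm − 1)ρ = 1 + 2rρ. If clustering is ignored, the true type I error is 2[1 − Φ(1.96/√DE)].

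| r | ρ | Design effect | Effective n of 4000 | Detectable reduction | Type I error |
|---|---|---|---|---|---|
| 5% | 0.1 | 1.01 | 3960 | 3.6 | 5.1% |
| 10% | 0.3 | 1.06 | 3774 | 3.7 | 5.7% |
| 20% | 0.5 | 1.20 | 3333 | 4.0 | 7.4% |
| 20% | 1.0 (extreme) | 1.40 | 2857 | 4.3 | 9.8% |

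The detectable reduction stays below 5 points in every row.

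**The case against.** **The covariate list is open.** It is given as examples, so a reader who infers that the models exclude hospital goes further than the text. A final covariate list is also ordinary analysis-plan content. This stands as far as the wording goes: hospital is not named, which is different from ruled out. But the opening is limited to patient-level confounders, and hospital is not one. Followed as written, the model has no site term.

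**The model already handles time.** A steady drift in site mix is largely absorbed by the time term, and part of any remaining shift by insurance, race, age and risk factors. This also stands. It would be wrong to infer that any drift in volume between sites will show up as a pathway effect. What remains is an abrupt change near implementation, and the article gives no sign that one occurred.

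**The text mostly speaks of patients.** A reader might infer that every visit is treated as an independent patient and that returns are counted twice. The article says neither. Eligibility, outcomes and sample size refer to patients, the registry is described in terms of patients, and Outcome Measures separates the index visit from recurrent visits and non-index admissions. The word encounters appears only in progress counts. Double counting is something the entry criteria permit, not something the article states.

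**The consequences are modest.** The magnitudes rest on assumed inputs, and no stated figure is overturned. That is correct. The case for change is that the protection is nearly free, not that a large error has been shown.

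**Conclusion.** The point holds in a limited form. The outcome models name only patient-level confounders and time terms, in a study whose three sites plausibly differ in admission rate. A change in site mix around implementation that those terms do not absorb would bias the intervention effect. Its size depends on unknown site rates: about 1 to 2 points for a 5 to 10 point shift under assumed rates of 60/45/20%, and as little as 0.3 to 0.6 points if the sites differ by only 5 points from one to the next. That the mix did shift is not shown.

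The secondary point is that the unit is not fixed. Patients and encounters are both used for accrual, and no rule says whether a returning patient enters again. If all encounters were analysed without allowance for clustering, the type I error would be about 5.1 to 7.4%, assuming 5 to 20% repeats and correlation of 0.1 to 0.5. The stated power is not affected on the two-proportion basis that reproduces it. The issue is bias and error rate, not power.

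**What to change.** 1. Add hospital as a fixed effect in all outcome models, binary and continuous, with site defined by the ED where the patient first presented. With three sites this costs two parameters and no new data.
2. State whether the planned 10,000 and the reported count of more than 5000 are patients or encounters.
3. Define the index visit as the first eligible visit per patient per period, and count visits within the following 30 days only as outcomes of that index.
4. If all encounters are analysed, as the main or a sensitivity analysis, use standard errors clustered on patient (robust variance or GEE).

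The cost is confined to the model and data-set rules. Restricting to first visits lowers the count: with 20% repeats, 4000 followed per period becomes 4000 × 0.80 = 3200. The detectable reduction is then about 3.97 × √(3333/3200) = 4.05 points, still below the stated 5.

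### The primary logistic model has no between-month variance although the intervention varies only with calendar time, so its P value and interval are too optimistic if admission practice varies by month

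*Protocol article*

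**What the plan says.** Study Design in the protocol article describes the study so: "This prospective pre-post interrupted time series design compares the risk stratification of patients with acute chest pain before and after implementation". Under Study Timeline the two "cohorts will each accrue patients with acute chest pain for 1 year, with a 3-month wash-in period". The abstract uses the word controlled, but the methods describe no concurrent comparison series.

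Under Outcome Measures, "The primary outcome will be hospitalization rate at 30 days for patients presenting with acute chest pain". Statistical Analyses specifies "Logistic regression models, which include potential patient-level confounders such as age, sex, race, ethnicity, insurance status, and ACS risk factors", together with an intervention indicator. Against secular trends it adds that "we will include the time since the start of the study in the models, as well as the time by intervention interaction", and it says of this model: "This will allow us to assess the effect of the HEART Pathway implementation on the proportion of patients hospitalized". Significance is judged at P<0.05.

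The section names no month-level random effect, robust or clustered standard error, overdispersion scaling or autocorrelation term. The one diagnostic it gives is "Residuals will be examined to ensure the model assumptions (linearity, homoscedasticity, and normality) are met". This stands in the paragraph on continuous outcomes and does not list independence.

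**The concern.** In this design, calendar time alone decides whether a patient is pre or post. Patients seen in the same month share bed capacity, staffing, provider rotation and local policy. When those factors move the admission rate off its trend in a given month, the whole month moves together, and the movement passes straight into the intervention coefficients.

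Ordinary logistic standard errors assume that, given the covariates and the fitted trend, each patient is an independent draw. They shrink with the number of patients (about 10,000), although the relevant replication for a calendar shock is the number of months (24). Time and time-by-intervention terms remove a trend from the mean. They do not put the remaining month-to-month scatter into the variance.

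The study's main claim, that implementation reduced hospitalization, would rest on this interval and P value. The other outcomes use the same kind of model.

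**Working it through.** **Inputs from the article.** Pre-period hospitalization is 53% and the test is two-sided at 5% (Sample Size). On numbers: "A sample size of approximately 10,000 patients, (5000) pre- and (5000) post-intervention, is anticipated", with 4000 per period expected to have follow-up. Accrual is 12 months in each period with a 3-month wash-in (Study Timeline).

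**Assumptions.** The wash-in lies between the cohorts and is excluded. Time is linear within each period. There is no intervention effect and no underlying trend. The level change at the start of the post period is the test of interest. The month-to-month SD is varied, because the documents give none. Patient covariates were not simulated.

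**1. The plan's own figure.** The article says reductions of less than 5% are detectable with 90% power. For two independent proportions, the detectable difference is (1.96 + 1.28) × √[(p₁q₁ + p₂q₂)/n].
- n = 4000: 3.24 × √[(0.2491 + 0.2500)/4000] = 0.036, or 3.6 points.
- n = 5000: the same formula gives 3.2 points.

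The figure reproduces as a comparison of independent patients, with no design effect.

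**2. Sampling noise in one month.** Patients per month: m = 5000/12 ≈ 417. The binomial SD of a monthly rate is √(0.2491/417) ≈ 2.4 points. A shared month effect of similar size therefore about doubles the variance.

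**3. Variance inflation and true size.** For a month SD of s (as a proportion) and independent months, inflation is D = 1 + (m − 1)s²/[p(1 − p)], and the true size is 2[1 − Φ(1.96/√D)].
- s = 0.01: D = 1 + 416 × 0.0001/0.2491 = 1.17; size about 7%.
- s = 0.02: D = 1.67; size about 13%.
- s = 0.03: D = 2.50; size about 22%.

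Size reaches 10% when D = (1.96/1.645)² = 1.42, that is at s ≈ 1.6 points.

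**4. Simulation under a true null.** The stated model (time, intervention, time by intervention) was fitted with model-based standard errors at 5000 per period. Ranges span separate sets of runs.

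| Month SD (points) | D | Closed form | Independent months | Lag-1 autocorrelation 0.5 |
|---|---|---|---|---|
| 0 | 1.00 | 5% | 4% | not applicable |
| 1 | 1.17 | 7% | 6-8% | 9% |
| 2 | 1.67 | 13% | 12% | 20-22% |
| 3 | 2.50 | 22% | 19-23% | 33-34% |

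At 4000 per period the level test rejects 11.6% (SD 2) and 18.0% (SD 3) with independent months, and 17.1% and 30.8% with autocorrelation 0.5. A joint level-and-slope test at 5000 per period rejects 16.1% (SD 2) and 30.4% (SD 3) with independent months.

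**5. Scaled variance.** There are 24 months and 4 mean parameters, hence 20 degrees of freedom. At 5000 per period and SD 2-3, Pearson scaling with a t reference on 20 df gives about 3-6% with independent months. With autocorrelation 0.5 it still gives about 11-16%.

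**6. Cost in precision.** With the stated time terms and no month variation, the detectable level change at 90% power is about 7.9 points at 5000 per period. That already exceeds the two-proportion figure because of the trend terms, which is a separate matter. Multiplying by √D gives 7.9 × 1.29 ≈ 10.2 points at SD 2 and 7.9 × 1.58 ≈ 12.5 points at SD 3.

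**The case against.** The strongest reply is that the defect is inferred from silence. Statistical Analyses lists mean-model terms and does not name a standard-error method. It does not say that errors are independent, that time is linear, or which coefficient decides the primary outcome. The article condenses a fuller protocol, and an analysis plan that is not shown may specify a robust or time-series variance. This stands as a caution: if such a method is already fixed elsewhere, the sponsor need only say so. It does not remove the point. The article states a model and a significance threshold, presents them as the answer to secular trends, and justifies the sample size by a figure that reproduces for independent patients. Read as written, logistic regression uses model-based errors.

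A reader might infer that ordinary month-to-month variation will be mistaken for a pathway effect. The documents do not support that. The inflation depends on a monthly SD that they do not give, and at 1 point it is small. Even at 3 points most null series are not rejected. The test is two-sided, so only about half of false rejections would look like a benefit.

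Two further limits stand. The planned covariates may absorb month-to-month variation due to case mix, so only the remainder, mainly admission practice, counts. The inflation was worked out only for a 53% outcome. It will be smaller for rarer events: with an assumed 5% rate and a logit-scale month SD of 0.10, D = 1 + 417 × 0.0475 × 0.01 ≈ 1.20 and size is about 7%.

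The article discloses secular trends and provider maturation as threats under Limitations. Disclosure does not widen the interval.

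**Conclusion.** The concern holds in conditional form. As written, the primary analysis of a calendar-assigned intervention carries no between-month variance. If admission practice varies between months beyond trend and covariates, the stated 5% level is not met and the interval is too narrow. Size doubles at a residual month SD of about 1.6 points with independent months, and grows further with autocorrelation. All of this rests on assumed SDs, linear time, 53% hospitalized and about 417 patients per month.

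It does not follow that the 5% level is certainly breached in this health system, that a significant result would be spurious, or that the secondary outcomes suffer to the same degree. The point merits a change to the stated method because the primary conclusion depends on it and the change is cheap.

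**What to change.** Keep the mean model in Statistical Analyses. Base the primary confidence interval and P value on variation between calendar months, by a random calendar-month intercept or a Pearson-scaled variance, with a t reference on about 20 degrees of freedom.

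Check month-level residual autocorrelation and model it if present, for example with AR(1) month effects, because scaling alone is then only a partial remedy. The AR(1) option was not itself simulated here, and 24 months give limited information on serial correlation. Report the estimated month SD and autocorrelation with the result.

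Use the same structure for the other outcomes. A seasonal term, a hospital term or clustering on repeat patients does not replace it, because none of these supplies the shared non-seasonal month component.

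The cost is a sentence or two of analysis wording and a few lines of SAS, with no new data. If months vary, intervals widen and the detectable effect grows. If they do not, there is little or no loss: the scaled test is slightly conservative, at about 3%.
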